### 2.2. Inclusion Criteria

Eligible patients should fully meet the Rome IV criteria [2]:(1)Onset of the following symptoms for at least 6 months before enrolment and symptoms within the past 3 months that meet the following criteria [2, 52]:Two or more of the following symptoms: (a.) difficulty passing stool, at least 25% of defecations; (b.) lumpy or hard stool, at least 25% of defecations (Bristol Stool Form Scale (BSFS) types 1 or 2 (Appendix 3) [53]); (c.) incomplete defecation in at least 25% of defecations; (d.) sense of anorectal obstruction in at least 25% of defecations; (e.) need for manual assistance for defecation (such as using fingers to assist with defecation or pelvic floor support) in at least 25% of defecations; and (f.) fewer than 3 spontaneous bowel movements (SBMs) per week.Loose stool rarely occurs without the use of laxatives.Insufficient stools are rarely present without the use of laxatives.(2)Willing to sign the informed consent form (Appendix 4)(3)The volunteers involved in this study will be patients with chronic constipation aged 18–65 years. For patients aged from 18 (exclusive) to 50 (inclusive) years, the result of stool tests (including occult blood) conducted during the screening period must be normal or abnormal but determined to be clinically irrelevant by the investigators. For patients aged 50 (exclusive) to 65 (inclusive) years, the result of a colonoscopy performed at a tertiary or higher-level hospital within the past 6 months must be normal or abnormal but determined clinically irrelevant by the investigators.

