### 2.7. Prohibited Confounding Interventions

The following treatments are prohibited during the study: (1) probiotics, prebiotics, and foods containing probiotics (such as yoghurt) other than the *Lactobacillus plantarum* used in this study; (2) antianxiety, antidepressants, and other psychotropic drugs; and (3) other substances designed to improve intestinal symptoms.

In addition, antibiotics will be monitored during the study, and normal dietary habits will be recommended. All concomitantly used substances/drugs related to defecation should be recorded daily in the online defecation diary (Figure 2), and explanations are needed.

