### 2.8. Primary Outcome

A defecation diary developed with reference to the literature [32, 53–56] will be completed daily online by the participants (Figure 2). Based on the diary, the changes in primary and some of the secondary outcomes from day 0 (week 0) to day 42 (week 6) will be evaluated.The primary outcome measure is the weekly mean frequency of complete spontaneous bowel movements (CSBMs) [32, 54, 55].

A CSBM is defined as the ability to achieve a complete bowel movement without the use of any drugs or other auxiliary measures during the previous 24 hours. Based on the diary (Figure 2), the weekly mean frequency of CSBMs from day 0 (week 0) to day 14 (week 2), day 28 (week 4), and day 42 (week 6) will be evaluated [32, 54, 55] (Table 1).

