### 2.9. Secondary Outcomes

Based on the diary (Figure 2), the changes in the percentage of volunteers with a weekly mean frequency of CSBMs ≥3 [32, 54, 55], changes in the weekly mean frequency of spontaneous bowl movements (SBMs) [32, 54–56], weekly mean stool appearance score [53], weekly mean difficulty of passing stool score, and weekly percentage of volunteers who use auxiliary measures to assist with defecation (WPUAMA) will be evaluated each week from day 0 (week 0) to day 14 (week 2), day 28 (week 4), and day 42 (week 6). An SBM is defined as a bowel movement achieved without the use of any drugs or other auxiliary measures during the previous 24 hours [32, 54, 55] (Table 1).The Patient Assessment of Constipation Quality-of-Life (PAC-QOL) questionnaire (Appendix 5 [56, 57]) will be used to evaluate the QOL score on days 0, 14, 28, and 42.The Depression, Anxiety and Stress Questionnaire (DASS-21) [58, 59] (Appendix 6) will be completed online on days 0 (baseline), 14, 28, and 42 and used to assess the participants' emotional status (depression, anxiety, and stress) within the past week (Table 1).For the indicator of the gut microbiome, DNA will be extracted from the stool samples with the QIAamp Fast DNA Stool Mini Kit (Qiagen, Hilden, Germany) according to the manufacturer's instructions, and the quality of DNA will be examined using agarose gel electrophoresis and a NanoDrop spectrophotometer. Shotgun metagenomic sequencing will be performed on all samples using an Illumina HiSeq 2500 instrument. Libraries will be constructed from DNA fragments with a length of ∼300 bp; paired-end reads will be generated by sequencing 150 bp in the forward and reverse directions. Meanwhile, the metagenomic analysis will include several parts: the analysis of alpha diversity and beta diversity in each group to understand whether the differences in the microbiota compositions of groups are significant and a comparison of the taxonomic characteristics of the study group and the control group at the level of phylum, genus, and species to identify specific genes related to the individual differences of constipation. Metagenomic biological pathway analysis will be used to evaluate the effect of probiotics on the function of gut metagenomics in patients with constipation and to explore the metagenomic biological pathways contributing to the mechanism underlying the effect of probiotics on the treatment of constipation.For the indicator of the faecal metabolome, stool samples will be extracted using the protein precipitation method, and the supernatant will be transferred to sample vials for LC-MS/MS analysis. The original data will be subjected to peak alignment, retention time correction, and peak area extraction using the XCMS-Plus program. The structure of metabolites will be identified by accurate mass matching (<5 ppm) and two-level spectrum matching, and the METLIN database will be retrieved. We will then delete data with missing values > 50% in the group, normalize the data, and conduct multidimensional statistical analysis, including unsupervised principal component analysis (PCA), supervised partial least squares discriminant analysis (PLS-DA), and potential differentially abundant metabolite analysis. The metabolomic analysis might further identify the potential differentially abundant metabolites of probiotics in the treatment of constipation, and a correlation analysis between the gut microbiota and metabolites will be performed.

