### 2.15. Statistical Analysis

The intention-to-treat (ITT) analysis will be conducted between the two groups. Then, the following four data sets will be used for the per-protocol (PP) analysis: (1) the data from all participants who completed the follow-up and (2) a subgroup analysis regarding levels of compliance (≥80%, 60–80%, and <60%) to validate the robustness of the results. The hypothesis will be tested using the methods described below during the ITT and PP analyses.

First, the Wilcoxon signed-rank sum test will be used for the outcome measures, including the weekly mean frequency of CSBMs, weekly mean stool appearance score, weekly mean difficulty of passing stool score, weekly mean frequency of SBMs, QOL score, and emotional status score, at each observation point to analyse the intergroup differences in each outcome measure. The chi-square (*χ*^2^) test will be used for the outcome measures, namely, the percentage of volunteers with a weekly mean frequency of CSBMs ≥3 and WPUAMA, at each observation point. In the analyses, the *P* value indicating statistical significance will be set to 0.05.

Then, the Kruskal–Wallis rank sum test will be used for multiple comparisons of outcome measures, including the weekly mean frequency of CSBMs, weekly mean stool appearance score, weekly mean difficulty of passing stool score, weekly mean frequency of SBMs, QOL score, and emotional status score, and the *χ*^2^ test will be used for multiple comparisons of outcome measures, including percentage of volunteers with a weekly mean frequency of CSBMs ≥3 and WPUAMA, at each observation point to identify the intragroup changing trends in consecutive phases, namely, pre-, during, and postprobiotic administration. In the analyses, the *P* value indicating statistical significance will be adjusted to 0.05/[*k* (*k* −1)/2], where *k* is the number of sample groups included in the comparison.

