**Figure 2 fig2:**
[figure not shown]
Defecation diary.

**Table 1 tab1:** Study and follow-up schedule.

Item		Screening period (preadministration observation period)		Observation period during administration		Postadministration observation period
		Visit 0	Visit 1	Visit 2	Visit 3	Visit 4
		(Days −14 to −1)	Day 0	Day 14	Day 28	Day 42
Collection of volunteers' basic information	√					
Screening	√					
Signing informed consent form	√					
Stool test (including occult blood)	√					
Defecation diary	Completed online daily					
Primary outcomes	Weekly mean frequency of CSBMs		√	√	√	√

Secondary outcomes	Weekly mean frequency of CSBMs ≥3		√	√	√	√
	Weekly mean frequency of SBMs		√	√	√	√
	Weekly mean stool appearance score		√	√	√	√
	Weekly mean difficulty of passing stool score		√	√	√	√
	Weekly mean stool appearance score		√	√	√	√
	Weekly mean difficulty of passing stool score		√	√	√	√
	WPUAMA		√	√	√	√
	Quality-of-life score		√	√	√	√
	Emotional state score		√	√	√	√
	Gut microbiome		√		√	√
	Faecal metabolome		√		√	√

Safety measures	Adverse events (AEs)			√	√	√
	Serious adverse events (SAEs)			√	√	√

Verification of compliance with the intervention					√	
Concomitant medications			√	√	√	√

*Note*. Except for the quality-of-life score and emotional state score, the other outcome measures are calculated from the defecation diary.

**Table 2 tab2:** The comparisons of methodologies among the present and previous RCTs related to the effect of probiotics on chronic constipation.

Study	Design	Allocation concealment/Blinding/ITT analysis/Description of withdrawals or dropouts	Sample size (probiotics:control)	Population	Age (years)	Diagnostic criteria	Intervention	Comparator	Probiotic strain	Outcomes	Daily dosage (CFUs)	Study stage (duration)
Agrawal [68]	Randomized, double-blind, controlled, parallel group study	Yes/Yes/Yes/Yes	17/17	Irritable bowel syndrome with constipation in females	20–69	Rome III criteria for constipation predominant IBS	A fermented milk containing probiotics	A milk-based nonfermented dairy product	*Bifidobacterium lactis*	Abdominal distension, gastrointestinal transit, abdominal symptoms, and bowel habit	1.25 × 10^10^	Screening period/baseline (11 days), administration period (28 days), postadministration period (7 days)

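### Auxiliary-measure use (WPUAMA) is analysed only as yes/no per volunteer per week, so a reduction short of stopping is not seen on this secondary outcome and power can be lost

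*Protocol article*

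**What the plan says.** All references are to the protocol article.

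- Section 2.9 (Secondary Outcomes) defines the outcome through its name: "weekly percentage of volunteers who use auxiliary measures to assist with defecation (WPUAMA) will be evaluated each week". That is one status per volunteer per week, summarised as a percentage.
- Section 2.15 (Statistical Analysis) gives chi-square between the arms to the two percentage outcomes, "namely, the percentage of volunteers with a weekly mean frequency of CSBMs ≥3 and WPUAMA, at each observation point", and chi-square again for the within-group comparisons. No count, days-per-week or share-of-movements version of auxiliary use is listed.
- The data are daily. Section 2.8 has the diary completed online each day, and the note to Table 1 says "Except for the quality-of-life score and emotional state score, the other outcome measures are calculated from the defecation diary". Section 2.7 adds: "All concomitantly used substances/drugs related to defecation should be recorded daily in the online defecation diary (Figure 2), and explanations are needed".
- Sections 2.8 and 2.9 let a movement count as a CSBM or SBM only if no drug or other aid was used in the preceding 24 hours.
- Section 2.2 grades one entry symptom on a finer scale than any/none: "need for manual assistance for defecation (such as using fingers to assist with defecation or pelvic floor support) in at least 25% of defecations".
- Section 2.12 bases the sample size on CSBM frequency alone. No expected rate and no power are given for WPUAMA.

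**The concern.** If the product makes defecation easier, a plausible pattern is that users need aids on fewer days, with only some giving them up. A yes/no status per week registers the second change and not the first. Someone who used an aid on 7 days before treatment and on 1 day at day 28 is a user both times.

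The other dichotomised outcome, CSBMs ≥3, has a full-scale counterpart: CSBM frequency, which is the primary outcome and has a rank test. The remaining diary measures and the questionnaire scores also have rank tests. Auxiliary use is the only clinical outcome kept solely as a percentage. At stake is a report of no difference in reliance on aids when volunteers have cut down without stopping.

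**Working it through.** **1. The plan's own figure.** The only sample-size figure concerns the primary outcome. With difference 3, SD 6, two-sided alpha 0.05 and power 0.80: n = 2 × (1.960 + 0.842)² × 6² / 3² = 62.8, so 63 per group, as section 2.12 states. It does not depend on WPUAMA. The planned 100 per group is used below.

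**2. Is the finer count available?** A movement cannot be classed as an SBM unless aid use in the previous 24 hours is known. With a daily diary, days of use per week (0–7) should therefore be derivable. This is an inference, because the diary (Figure 2) is not shown in the text reviewed.

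**3. Simulation set A (all rates assumed).** Days of use x ~ Binomial(7, p), with p varying between people as a beta distribution and within-person correlation 0.2 or 0.4. The control mean was set to give a chosen percentage with x > 0, and the daily odds of use were multiplied by 0.4 under treatment. There were 1,500 trials per setting, two-sided 0.05, 100 per group. Chi-square on x > 0 was compared with rank-sum on x.

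| Control users in the week | Correlation | Chi-square | Rank-sum | Gain (points) |
|---|---|---|---|---|
| 50% | 0.2 | 70% | 81% | 11 |
| 50% | 0.4 | 45% | 55% | 10 |
| 70% | 0.2 | 82% | 96% | 14 |
| 70% | 0.4 | 50% | 74% | 24 |
| 85% | 0.2 | 82% | 99% | 17 |
| 85% | 0.4 | 47% | 78% | 31 |

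At 20–30% users the gain is about 2 to 6 points. With 80 per group (20% drop-out), gains are 13 to 28 points at 50% users or more and 3.5 to 4.3 points at 30%.

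**4. Simulation set B (different assumptions).** Mean daily-use probabilities were set directly, with correlation 0.2, 0.4 and 0.6, 4,000 trials per setting and 100 per group.

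| Daily use, control vs probiotic | Control users in the week | Chi-square | Rank-sum | Gain (points) |
|---|---|---|---|---|
| 0.70 vs 0.50 | 99 / 95 / 88% | 49 / 68 / 77% | 99.9 / 99 / 96% | 51 / 31 / 19 |
| 0.50 vs 0.35 | 93 / 84 / 74% | 66 / 67 / 63% | 97 / 87 / 77% | 31 / 20 / 14 |
| 0.30 vs 0.20 | 77 / 64 / 52% | 69 / 63 / 55% | 84 / 70 / 57% | 15 / 7 / 3 |
| 0.10 vs 0.05 | 36 / 27 / 20% | 74 / 61 / 50% | 75 / 61 / 50% | 1 / 0 / 0 |

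(Three values per cell: correlation 0.2 / 0.4 / 0.6. Gains are from unrounded powers.) At 0.05 vs 0.02 the two tests agree to within about 1 point.

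**5. Limiting cases, 100 per group.**

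- *Same share of users in each arm, fewer days under treatment* (users at 3–7 days against 1–3 days): chi-square rejects about 5–6% of the time, which is its false-positive rate. Rank-sum power is 24% with 30% users, 86% with 50% and about 100% with 80%.
- *Effect only on whether aids are used:* with 50% vs 30% users and the same days among users, chi-square has 83% and rank-sum 80%. If 30% of treated users stop and the rest are unchanged, rank-sum is worse by 0.8, 5.3 and 9.4 points at 30%, 50% and 70% users.

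**The case against.** **Chi-square is a correct test of a proportion.** This stands. A reader might infer that the analysis is invalid, and it is not. The cost is lost information on an unpowered secondary outcome. Nor is the lack of a stated reason or citation for the cut a fault, since a condensed article can leave that to the full documents.

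**Use may be rare, and then nothing is lost.** This largely stands. Section 2.7 prohibits other substances meant to improve intestinal symptoms, section 2.4 allows no constipation remedies during screening, and section 2.3 excludes people who need long-term constipation medication. Manual assistance is one of six entry symptoms, of which two are needed. But manual aids are not among the prohibited items, and no rate is given, so neither low nor high use can be assumed.

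**SBM frequency already carries the signal.** This stands in part. If movements are maintained and fewer are assisted, SBM frequency rises, and it has a rank test. A reader might infer that reduced reliance would go wholly unmeasured; the SBM definition shows otherwise. SBM frequency also moves with total bowel frequency, however, so it does not isolate reliance on aids.

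**A count of days has its own weakness.** Assisted days depend on how often a volunteer defecates, which the product is expected to change. For illustration, 3 movements a week with 50% assisted and 5 a week with 30% assisted both give 1.5 assisted movements. This is fair, but it affects the any-use percentage too. It argues for showing the assisted share as well.

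**The threshold and the count are inferred.** This stands. The text does not write any use, and section 2.7 speaks of substances and drugs. The 24-hour rule requires aid status when a movement occurs, but does not prove that aid use is logged on other days.

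**Conclusion.** The point holds as a minor, conditional one. On the natural reading, WPUAMA is yes/no per volunteer per week and has only a chi-square test, so a fall from daily to once-weekly use is no change on it.

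A reader might infer that power is lost whatever the data look like. The protocol does not support that, because it gives no rate of use and the answer turns on it. In set A the loss is about 10 to 31 points where at least half of controls use an aid weekly, and about 2 to 6 points at 20–30% users. If the product acts only by stopping use completely there is no loss, and chi-square is ahead by up to about 9 points. Set B shows how far this depends on the assumptions: with more than half of controls using aids, the loss runs from 3 to 51 points, and at 20–36% users it is about 1 point or less.

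The primary outcome and the sample size are untouched.

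**What to change.** - Keep WPUAMA with its chi-square test as the prespecified secondary outcome. Replacing or demoting it is not warranted, since it is the better measure if the effect is all-or-none and 130 patients were already enrolled when the article was written.
- In 2.9, state that WPUAMA means any use of an auxiliary measure in the week.
- In 2.9 and 2.15, add a supporting between-arm comparison of days per week with any auxiliary measure (0–7, from the existing diary) at each observation point, by the independent two-sample rank-sum test. Name that test in full, because 2.15 calls its between-group test a signed-rank test, which is for paired data.
- Report the assisted share of bowel movements beside it, because bowel frequency is expected to change.
- Confirm from the diary form that manual and other non-drug aids are recorded daily.
- Make the change before any unblinding. Section 2.5 allows unblinding for interim as well as final analyses.

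The cost is a few sentences and one extra supporting analysis, with somewhat less power than WPUAMA if the effect is all-or-none. If the diary records aids daily, no new data or volunteers are needed.

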We optimize the methodology from the following aspects: ① The general principle for a high-quality RCT is strictly obeyed through the participation of third-party independent companies or the DMT, including randomization, parallel control, blinding, allocation concealment, combination of ITT and PP analyses, consideration of withdrawals or dropouts, replication (enough observed study subjects), and other factors. ② The sample size (100 for each group) is obtained based on the expected difference in weekly frequency of CSBMs between the treatment group and control group, which is sufficient to ensure the reliability and accuracy of the results. The sample sizes in 33 of the 35 previous RCTs are dozens or even several participants, which is probably not sufficient to obtain an accurate result. ③ The latest Rome criteria (Rome IV for the present RCT) are suggested for the diagnosis of chronic constipation to avoid any other self-definition by researchers. ④ Multidimensional outcomes have been observed in the present RCT, including improvements in clinical symptoms, QOL score, emotional status score, and modifications in the gut microbiome and faecal metabolome, to produce a chain of evidence from causal improvements in metagenomic and metabolomic data to clinical symptoms and then to the emotional state and QOL. The outcomes are measured using accepted methods, e.g., BSFS [53], PAC-QOL [57], DASS-21 [58], next-generation sequencing, and LC–MS/MS analysis. Thus, the effects of probiotics on chronic constipation in the present study are more reliable and explainable. ⑤ Other key parameters, such as the study stage and duration, are also suggested.

In addition, the protocol is conducted to prove its feasibility and scientificity by studying the effects of *L. plantarum* P9 on chronic constipation. The study is articulated with a clear testable hypothesis stating that *L. plantarum* P9 improves the clinical symptoms and patient QOL by modifying the intestinal flora. Additionally, the safety of *L. plantarum* P9 will be assessed.

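### Seven clinical secondary outcomes are compared between arms at three post-baseline visits, each at an unadjusted 0.05 (21 tests), giving roughly a 10-30% chance of at least one false benefit

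*Protocol article*

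**What the plan says.** Section 2.15 applies a rank test to the frequency and score outcomes "at each observation point to analyse the intergroup differences in each outcome measure". For the two proportions, the chi-square "test will be used for the outcome measures, namely, the percentage of volunteers with a weekly mean frequency of CSBMs ≥3 and WPUAMA", again at each observation point. For all of these between-arm tests the P value "indicating statistical significance will be set to 0.05".

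Section 2.9 and Table 1 define the secondary outcomes. Five come from the diary: CSBM of at least 3 per week, SBM frequency, stool appearance, difficulty of passing stool, and use of auxiliary measures (WPUAMA). Two come from questionnaires. The PAC-QOL "will be used to evaluate the QOL score on days 0, 14, 28, and 42". The DASS-21 is "used to assess the participants' emotional status (depression, anxiety, and stress) within the past week", on the same four days. The post-baseline visits are days 14, 28 and 42.

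Alpha is corrected in two other places. Section 2.15 divides 0.05 by k(k-1)/2 for within-arm trends across phases, and its paragraph on metagenomic and metabolomic data applies Benjamini-Hochberg.

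On what these tests are for, section 2.15 says: "The hypothesis will be tested using the methods described below during the ITT and PP analyses". The Discussion gives the hypothesis as *L. plantarum* P9 "improves the clinical symptoms and patient QOL by modifying the intestinal flora".

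**The concern.** The between-arm comparisons are the ones that use the randomisation and carry any claim of treatment effect. They are also the only family in section 2.15 with a flat 0.05 and no correction. The text names no key secondary outcome, no main visit for the secondary outcomes and no condition on the primary result. It does not describe them as exploratory either.

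The hypothesis in the Discussion reaches beyond the primary outcome. Quality of life is a secondary outcome, and so are all the symptom measures other than weekly CSBM frequency. A significant result among the 21 tests could therefore be reported as support for a hypothesis that the article says it tests, with a false-positive chance several times that of one test. The article also presents itself as methodological guidance for similar trials, so the rule may be copied.

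**Working it through.** **The plan's own figure.** Section 2.12 gives a difference of 3, SD 6, alpha 0.05 and beta 0.20, and arrives at 63 per group. Check: n = 2 x SD^2 x (z_0.975 + z_0.80)^2 / difference^2 = 2 x 36 x (1.960 + 0.842)^2 / 9 = 62.8, rounded up to 63. This agrees, and it shows that 0.05 is meant two-sided. The article states no family-wise error rate, so there is none to reproduce.

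**Inputs.**
- Outcomes: 7 (five from the diary, one QOL score, one emotional status score, as section 2.15 lists them).
- Post-baseline visits: 3. Tests: 7 x 3 = 21.
- Per-test level: 0.05 two-sided, hence 0.025 in the favourable direction.
- Correlation between test statistics: not given. Assumed 0.3 to 0.8.

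**Expected false positives, whatever the correlation.** Either direction: 21 x 0.05 = 1.05. Benefit: 21 x 0.025 = 0.525.

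**Independent tests, as an outer bound.** Either direction: 1 - 0.95^21 = 66%. Benefit: 1 - 0.975^21 = 41%.

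**Equal correlation r among all 21 statistics, global null.** With a shared standard normal component x, c = 1.96 and s = sqrt(1 - r):
- P(at least one benefit) = 1 - E[Phi((c - sqrt(r) x)/s)^21].
- For either direction, replace Phi(.) with Phi((c - sqrt(r) x)/s) - Phi((-c - sqrt(r) x)/s).

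| r | Either direction | Benefit |
|---|---|---|
| 0.3 | 55% | 29% |
| 0.5 | 43% | 22% |
| 0.7 | 30% | 15% |
| 0.8 | 23% | 11% |

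**A second correlation structure.** Simulation (400,000 draws per setting) with one correlation between outcomes crossed with another between visits gives:

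| Outcomes / visits | Either direction | Benefit |
|---|---|---|
| 0.3 / 0.3 | 60% | 33% |
| 0.5 / 0.5 | 49% | 25% |
| 0.5 / 0.7 | 44% | 22% |
| 0.7 / 0.7 | 35% | 18% |
| 0.8 / 0.8 | 27% | 13% |

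These run slightly higher than the equal-correlation values and lead to the same conclusion.

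**One visit only (7 tests, equal correlation 0.3 to 0.8).** Either direction 27% down to 15%; benefit 14% down to 7%. The repeated visits therefore account for a good part of the inflation.

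**After the fix.** Holm over seven outcomes at day 28 starts at 0.05/7 = 0.0071 and holds the family-wise error at or below 0.05 under any correlation. A fixed order at 0.05 per step does the same.

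The repetition of all tests in the per-protocol and compliance-level data sets is not counted above.

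**The case against.** The best case for the plan is this. One primary outcome is named, the trial is sized on it alone, and everything else is labelled secondary. Ordering or labelling of secondary outcomes is often left to a statistical analysis plan, and none is shown. Several of these outcomes must be strongly related: CSBM of at least 3 is a cut of the primary outcome, and every CSBM is also an SBM. That points to the lower rates.

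Much of this stands. The primary test is untouched, and the lower half of each range is plausible. The absence of an order would not be a finding by itself. What remains is that the article does not leave the matter open. It fixes 0.05 for each between-arm test and corrects two other families. An analysis plan that followed this text would reproduce the problem.

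Three stronger readings are tempting, and the document does not support them:
- **A 30-50% chance of a false benefit.** Rates of that size count differences in either direction, including those favouring placebo. For benefit, 21 tests give about 11-29% under equal correlations of 0.3-0.8, and only 41% even if all were independent.
- **27 tests, with depression, anxiety and stress separate.** Section 2.9 names the three domains, but section 2.15 lists one emotional status score. The count from the text is 21.
- **A licence for a secondary outcome to rescue a negative primary.** No passage says this. The rates above are also unconditional, not conditional on a negative primary result. The hypothesis joins symptoms and QOL with an 'and', does not mention mood, and is not a rule that any one of 21 results counts as success.

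**Conclusion.** The point holds for the secondary claims. Section 2.15 sets an unadjusted two-sided 0.05 for 21 between-arm tests of clinical secondary outcomes, while the article ties a tested hypothesis to symptoms and quality of life. Under a global null, at least one significant difference in either direction has a chance of roughly 25-55%. At least one significant benefit has a chance of roughly 10-30%, which is about 4 to 12 times the 2.5% of a single two-sided test.

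These figures rest on assumed correlations of 0.3-0.8, on approximately normal test statistics and on one emotional status score. The ranges move with the correlations, but no value examined comes near the single-test rate. The change should be made because it limits what the trial may claim from its secondary outcomes. It does not put the primary result in doubt.

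**What to change.** State in section 2.15 that between-arm comparisons of secondary outcomes support a confirmatory claim only if the primary comparison is significant. They are then tested at day 28, the visit used for sizing in section 2.12, either by Holm or in an order that the sponsor fixes. Report days 14 and 42 as exploratory estimates with 95% confidence intervals. Which outcomes come first is the sponsor's choice; what matters is that the order is fixed in advance. For the condition to work, the text must also say which single comparison of the primary outcome is meant.

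Alternatively, label all secondary outcomes exploratory and restrict the tested hypothesis to the primary outcome.

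Either version needs a few sentences and no new data. It should be in place before any unblinding, which section 2.5 allows at interim as well as final analysis. The downside is small: some nominally significant secondary results could no longer be claimed as confirmed.
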